### Randomization and assignment hiding

2.8

Using the “central randomized system of clinical research” of Guangdong Provincial Hospital of Chinese Medicine, 316 subjects will be randomly assigned to the treatment group and the control group according to the ratio of 1:1 by the method of regional group randomization. The personnel of Central Randomization System of Clinical Research of Guangdong Provincial Hospital of Chinese Medicine will be responsible for the random distribution of the included patients but they will not participate in the clinical treatment operations. After the participants are grouped, the therapist will be informed which group the patients are divided into, and then he will treat the patients in the group.

### Blinding method

2.9

Blinding methods will be applied to data statisticians and outcome evaluators throughout the trial. They will not able to obtain information regarding grouping and treatment of participants. Acupuncture and tuina belong to the external treatment of TCM, it is difficult to implement blind method for operators, so clinical therapists do not participate in data collection, statistics, and final outcome evaluation. For the treatment of patients, we will assign different patients to different treatment rooms where the beds are independent so as to avoid contact among patients. We separate personnel who separately in charge of random grouping, clinical treatment, data processing, and outcome evaluation completely, so as to ensure the authenticity of the outcome of the trial to the greatest extent possible.

### Interventions

2.10

Acupuncture in the treatment group will be performed by acupuncture doctors who have received unified clinical training of scalp acupuncture therapy, have obtained Certificates of Acupuncture, and have had clinical experience for >5 years. The tuina operations are all performed by clinical tuina therapists who have received training in the TJTX technique and have clinical experience of >3 years. In the control group, PT will be performed by rehabilitation therapists who have received unified training of PT and have had rehabilitation working experience for >3 years. In the treatment group, scalp acupuncture and tuina are both widely used in the clinical rehabilitation of patients with spasticity in post-stroke patients in TCM hospital. However, in the Chinese stroke rehabilitation treatment guidelines (2011 edition),^[22]^ which is the latest guide, PT (which performed in the control group) is recommended for the treatment of limb spasm after stroke. Both groups will receive 20 sessions (5 sessions per week) of treatment in 4 weeks.

#### Treatment group:

2.10.1

The treatment group will be treated with TJTX (30 minutes in total, 1/d) combined with MSA (6 hours in total, 1/d) and YNFJ (2/d).

##### Excising scalp acupuncture therapy

2.10.1.1

Supplies: needles (0.35 mm in diameter, 40 mm in length Hwato Brand, Suzhou Medical Appliance Factory, China), alcohol swabs (6 cm × 6 cm, HAINUO Brand, Qingdao Hainuo Bioengineering Co., Ltd., China), electronic acupuncture treatment instrument (KWD-8081, The Great Wall Brand, Changzhou Wujin Great Wall Medical Equipment Co., Ltd., China), aseptic cotton bud (HAINUO Brand, Qingdao Hainuo Bioengineering Co., Ltd., China).

Acupoints: Positioning Qianding (DU21), Baihui (DU20), and XinHui (DU22) point (Fig. 2).

**Figure 2 F2:**
[figure not shown]
Acupoints of scalp acupuncture.

The patient lies supine, while the acupuncturist sterilizes Qianding (DU21) with alcohol swabs, inserts the needle into Qianding (DU21) at a 30° angle with the skin, then inserts the needle into the acupoint slowly and smoothly until it is under the cap aponeurosis, penetrating the depth of 25 to 40 mm with the direction to Baihui (DU20). The connection between Qianding (DU21) and Baihui (DU20) is named Line 1. From the left and right 1 cun and 2 cun points of Qianding (DU21), there will be needling along the direction parallel to line 1. From the Positioning XinHui (DU22) point, the acupuncturist inserts the needle into XinHui (DU22) with the same technique as above, penetrating towards Qianding (DU21). The connection between XinHui (DU22) and Qianding (DU21) is named Line 2. From the left and right 1 cun points of XinHui (DU22), the needle direction parallels line 2. Eight needles are used per session.

After the needles have penetrated, we will use electronic acupuncture treatment instrument to connect the acupoints on both sides of Qianding (DU21) and both sides of Baihui (DU20) point, with an intermittent wave of 80 Hz frequency and an intensity of 1 to 10 mA; 30 minutes later, we remove the electric acupuncture. We then maintain the needles in the head for 6 hours during which time the patients receive physical therapy, 5 sessions a week over 4 weeks.

##### Tuina of Tong Jing Tiao Xing

2.10.1.2

Acupoints: Hegu (LI4); Quchi (lI11); Weizhong (BL40); Yanglingquan (SP9); Taichong (LR3); Zhongwan (RN12) (Fig. 3).

**Figure 3 F3:**
[figure not shown]
Acupoints of TJTX.

Treatment process: the participant lies in the healthy-side-up position. The therapist kneads the spine with palm down to sacrum along DU channels 5 times (3 minutes); the participant then lies in the supine position. Therapist rolls on participant's upper and lower limbs along 3 yang meridians of hand and 3 yang meridians of foot of the affected side 3 times (the upper limbs for 3 minutes and the lower limbs for 5 minutes, total of 8 minutes). Then the therapist slowly flexes and stretches the affected shoulder, elbow, wrist, and metacarpophalangeal joints, then presses Quchi (lI11) and Hegu (LI4) points to promote elbow extension, wrist extension, and finger movement. The therapist slowly flexes and stretches the hip, knee, ankle, and metatarsophalangeal joints, pressing the Yanglingquan (SP9) point to promote ankle dorsiflexion, and pressing Taichong (LR3) (SP9) point to promote the extension of the metatarsophalangeal joint. The patient is turned lie in the healthy-side-up position, and the therapist presses the Weizhong (BL40) point to promote knee flexion, performing each of these movements 5 times (about 16 minutes); the therapist grasps upper and lower limbs top-down of the affected side 3 times (about 1 minute); and the therapist presses the Zhongwan (RN12) point with the palm, and gradually presses it with the breath until the operator feels the beat under the palm, and keeps the pressure constant for 30 seconds, and then releases the hand quickly when the participant breathes out. This is repeated 5 times (about 3 minutes).

##### Yi Nao Fu Jian Fang

2.10.1.3

This prescription contains 9 Chinese herbal medicines, including Radix Paeoniae Rubra 5 g, Ligusticum chuanxiong 3 g, Puhuang 5 g, Pueraria 5 g, Sophora japonica 5 g, earthworm 5 g, safflower 3 g, Shencao 7.5 g, and Sanqi 4.5 g. Those are provided orally or nasally, 43 g per time, twice a day for 4 weeks.

##### Physical therapy

2.10.1.4

After electroacupuncture, the participants will receive following treatments. Muscle spasm control: placement of good limb position; reflex inhibitory pattern (RIP), influence tension posture (TIP), and control key points in Bobath technology; using sensory stimulation of Rood technology, inhibition of spasm through corresponding sensory stimulation; promote the emergence of separation movement: further promote the separation movement of the affected side of the limb using nerve facilitation technology, sports relearning, and other training; therapeutic training; sitting balance training, standing balance training, walking training, up and down stairs training, and others.

#### Control group

2.10.2

PT for the control group is the same as that of the treatment group.

### Outcome measurements

2.11

Multiple dimensions are selected to evaluate the patients so as to determine the therapeutic effect of ESA combined with TJTX and YNFJ on spasticity post-stroke. Table 1 shows the times of evaluation of this study.

**Table 1 T1:**
[figure not shown]
Research design schedule.

#### Primary outcome

2.11.1

##### The main outcome of this study is the modified Ashworth scale

2.11.1.1

The MAS will be used to evaluate muscle tone. The degree of spasm is divided into 0, I, I+, II, III, and IV levels according to the resistance felt by the evaluators during passive movement of the elbow and knee joints of hemiplegic patients in the resting state. The higher the score, the higher the degree of spasm.^[23,24]^ This will be evaluated at the—1st and at the 2nd and 4th weeks after randomization, and at the 3rd and 6th months after treatment.

#### Secondary outcomes

2.11.2

##### Simplified Fugl–Meyer assessment scale (FMA)

2.11.2.1

Functional rehabilitation will be assessed using the simplified FMA and the mini-mental state examination (MMSE). There are 50 items in the FMA, which are scored with 0 to 2 points, involving upper and lower limbs, with the highest score of 100 points. The higher the score, the better the motor function; the MMSE includes 5 items (orientation, memory, attention and calculation recall ability, and language ability) with a total score of 30. Higher score indicates better function. This is measured at the—1st and at 2nd and 4th weeks after randomization, and at the 3rd and 6th months after treatment.

##### Surface electromyogram root mean square (RMS) value

2.11.2.2

Surface electromyogram (sEMG) is a neurophysiological measurement method in which electrode plates are attached to the skin to record the activity of skeletal muscle. As an effective objective quantitative evaluation index of spasticity state after stroke, the sEMG analysis system (Model: SA7550, Nanjing Weisi Medical Technology Co., Ltd.) is used in this study to evaluate the biceps and triceps of the affected side of upper humerus and RMS of sEMG of the quadriceps femoris and hamstring. This item is measured at the—1st and the 2nd and 4th week after randomization.

##### Modified Barthel index (MBI)

2.11.2.3

The activity of daily living (ADL) is assessed by the MBI. There are 15 items in the Barthel Index with a total score of 0 to 100. A score of 0 indicates poor function, no independent ability, and all activities of daily living require help. A score of 100 indicates that the patient's basic activities of daily life are in good condition, and the help of others is not needed (the patient is not only able to control defecation, but can eat, dress, and bathe unaided). Lower scores demonstrate worse survival status. This will be evaluated at the—1st and at 2nd and 4th week after randomization, and at the 3rd and 6th months after treatment.

##### Stroke specific quality of life scale (SS-QOL)

2.11.2.4

SS-QOL is used primarily to evaluate the life status of patients after stroke. This table includes 12 fields, including mood, energy, vision, language, social role, and others. There are 49 items in total. Each item is scored with a 5-level scoring method (1–5 points), and the scoring range is 0 to 245 points. Higher score indicates better living conditions. This is evaluated at the—1st and at the 2nd and 4th week after randomization, and at the 3rd and 6th month after treatment.

##### Health scale of traditional Chinese medicine (SF-HSTC)

2.11.2.5

SF-HSTC consists of 28 items, which are classified into 5 aspects, including the social environment, physical function under natural environment, spirit, and ability of communication with people, adaptability of natural environment. The score range is 0 to 130. The higher the score, the worse the health status. This table requires the evaluation of the patients’ condition of the past month, so it is only evaluated during the baseline period and at the 4th week after randomization as well as the 3rd and 6th months after the end of treatment.

##### Visual analogue scale (VAS)

2.11.2.6

VAS pain score is widely used for subjective pain evaluations. The modified evaluation involves marking the 2 ends of a 100-mm line as 0 and 10, respectively. Zero means no pain and 10 means the most pain. Patients can draw a mark on the line according to the subjective evaluation of their own pain. The distance from 0 to the marker indicates the degree of pain. This will be measured at the—1st and at the 2nd and 4th weeks after randomization, and at the 3rd and 6th months after treatment.

##### Hamilton depression scale (HAMD)

2.11.2.7

The HAMD is the most generally used scale for clinical depression assessment. There are 17 items in the scale, and the score range is 0 to 52. The higher the score, the more severe the depression. This will be measured at the—1st and at the 2nd and 4th weeks after randomization, and at 3rd and 6th months after treatment.

### Adverse events

2.12

During the experiment, we will ask the participants to report adverse events in the course of treatment, including dizziness, nausea, palpitation, collapse, pain, and itching at the acupuncture site, as well as bleeding and persistent pain at the acupuncture site or after acupuncture. The patient may have increased pain during the Tuina, or bruise, swelling, persistent pain of the limb after the Tuina. Nausea, vomiting, diarrhea, acid regurgitation, and other symptoms may occur after oral administration of traditional Chinese medicine. We also require the therapists to actively report stuck, bent, and broken needles in the acupuncture treatment and the skin abrasions of the patients during the tuina process. Researchers need to record the occurrence times, situations, grades, corresponding treatment methods, and the relationship between the time of adverse reactions and treatment measures in case report forms.

### Sample size calculation

2.13

The sample size calculation will be conducted based on a study by White.^[25]^ This was a study using the modified Ashworth spasticity scale (MAS) as the main outcome, that showed that the total effective rate of physical therapy for spasticity of post-stroke was 45.5%.^[26]^ Our early clinical observation suggested that the total effective rate of the comprehensive rehabilitation treatment program of TCM in this study would be 65%. According to comparison of independent sample rates between 2 groups to calculate sample size: *α* = 0.05, *β* = 0.1, power = 90%, 132 participants in each group will be recruited. Considering an estimated 20% dropout rate, a total size of 158 cases in each group will be recruited.

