### Inclusion criteria

2.5

Patients need to meet the following criteria: the diagnostic criteria of stroke^[21]^; symptoms of increased limb muscle tension, with the modified Ashworth Scale (MAS) score grade 1–2; the course of disease is within 2 weeks to 6 months; age 35–70 years, male or female; conscious and have stable vital signs; and participants or family guardians provide written informed consent.

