### Data analysis contents and methods

2.15

Statistical analysis will be conducted by GPHCM's Key Unit of Methodology in Clinical Research. We will use bilateral test with a significance level of *α* = 0.05, performed using SPSS (SPSS, SPSS Inc., Chicago, IL) version 21.0.

For efficacy evaluation indexes, the data sets of per-protocol analysis (PP) and intention to treat analysis (ITT) will be used. A safety analysis set (SS) will be used for safety evaluation and analysis. Depending on the data type, appropriate statistical methods will be used. First, descriptive statistics will carried out for baseline characteristics of patients. The efficacy evaluation index data are repeated measurement data that can be used for the analysis of variance of repeated measurement. Due to the data missing values caused by withdrawal, the method of multiple filling will be used in ITT analysis. If necessary, the method of missing value processing provided by SPSS version 21.0 can be used to replace data, and various methods will be selected according to the actual situation. For safety evaluation analysis, we will test and compare the incidence of adverse reactions between 2 groups. The severity of adverse reactions and the degree of causality with treatment will be considered in comparison. If the number of adverse reactions is large, the relationship with treatment duration and baseline characteristics will be analyzed.

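### The 90% power is computed for a binary effective rate that is not among the trial's outcomes, so it does not apply to the repeated-measures ANOVA of MAS grades, the only efficacy test named

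*Protocol article*

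**What the plan says.** All references are to the protocol article.

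- **Sample size (2.13).** The control assumption is that "the total effective rate of physical therapy for spasticity of post-stroke was 45.5" per cent, taken from a cited study that had MAS as its main outcome. The treatment assumption is that the "total effective rate of the comprehensive rehabilitation treatment program of TCM in this study would be 65" per cent, from the team's own clinical observation. The method is given as "According to comparison of independent sample rates between 2 groups to calculate sample size", with the result "power = 90%, 132 participants in each group will be recruited". Then: "Considering an estimated 20% dropout rate, a total size of 158 cases in each group will be recruited".
- **Primary outcome (2.11.1.1).** This is the MAS, in six ordered levels (0, I, I+, II, III, IV), graded "according to the resistance felt by the evaluators during passive movement of the elbow and knee joints of hemiplegic patients in the resting state". It is recorded at baseline, at weeks 2 and 4, and at months 3 and 6 after treatment.
- **Secondary outcomes (2.11.2).** These are scales and the surface electromyogram value. No effective or responder rate is among them.
- **Analysis (2.15).** Tests are two-sided at 0.05, and methods are to suit the data type. The one efficacy method named is in this sentence: "The efficacy evaluation index data are repeated measurement data that can be used for the analysis of variance of repeated measurement".

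**The concern.** A power statement holds for one endpoint, one test and one assumed effect. In 2.13 the endpoint is binary (effective or not) and the test compares two independent proportions. In 2.11.1.1 the endpoint is an ordinal grade at two joints over five visits. In 2.15 the named test is a repeated-measures ANOVA, which yields at least a group effect and a group-by-time effect. Nothing in the article carries the 45.5% and 65% over to a difference in MAS grades, and no comparison of effective rates is listed.

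The stake is how the result will be read. A reader will take the 90% as the trial's chance of detecting the assumed benefit on its primary outcome. The article supports that only for a response variable it does not define. If the ANOVA is reported as the main result, the 90% says nothing about it. If an effective rate is reported instead, its definition will have been chosen outside the published plan.

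**Working it through.** **1. Reproduce the plan's figure.** Inputs: p1 = 0.455 and p2 = 0.65 (2.13); two-sided alpha 0.05 (2.15); power 0.90 (2.13); 1:1 allocation (2.8).

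Unpooled two-proportion formula: n = (1.960 + 1.2816)² × [p1(1 − p1) + p2(1 − p2)] / (p2 − p1)²

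- p1(1 − p1) = 0.455 × 0.545 = 0.2480
- p2(1 − p2) = 0.65 × 0.35 = 0.2275
- sum = 0.4755; (0.195)² = 0.03803; (3.2415)² = 10.507
- n = 10.507 × 0.4755 / 0.03803 = 131.4, so 132 per group

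This matches exactly. The pooled-variance formula gives 135, and by that formula 132 per group has 89.4% power. The 90% is therefore the power of a two-proportion test.

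**2. Set the sections side by side.**

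| | 2.13 | 2.11.1.1 and 2.15 |
|---|---|---|
| Endpoint | effective: yes or no, not defined | MAS grade, six ordered levels |
| Joints | not stated | elbow and knee |
| Visits | not stated | baseline, weeks 2 and 4, months 3 and 6 |
| Test | two independent proportions | repeated-measures ANOVA |
| Effect assumed | 45.5% against 65% | none given |

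**3. Can the power of the named analysis be found?** No. It needs a MAS difference at each visit, a standard deviation and a within-patient correlation, and the article gives none of them.

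**4. Range under assumptions (illustrative only).** For one two-group comparison of means at 132 per group, power = Φ(d × √(132/2) − 1.960), with √66 = 8.124 and d the assumed standardised difference:

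- d = 0.2: Φ(−0.335) = 37%
- d = 0.3: Φ(0.477) = 68%
- d = 0.4: Φ(1.290) = 90%
- d = 0.5: Φ(2.102) = 98%

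If the two rates came from cutting a normal variable with equal spread in both groups, the implied difference would be z(0.65) − z(0.455) = 0.385 + 0.113 = 0.50, so a single-visit comparison would have more than 90% power. With a peak difference of 0.5 at week 4, 132 per group, a common visit correlation of 0.3 to 0.7, and an effect that persists, fades or is gone by month 6, approximate power over the five visits runs from 46% to 99% for the group effect and from 83% to nearly 100% for group-by-time. The same two rates are thus compatible with power on either side of 90%, depending on the contrast and on how the effect evolves.

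**The case against.** **The wording of 2.15 is permissive.** It lets the method depend on data type, says the data can be used for repeated-measures ANOVA, and never labels that analysis primary. This stands: the article does not exclude a comparison of rates. But it does not list or define one either, so the 90% remains without a planned test.

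**The detail may sit in an analysis plan.** The choice of joint, decisive visit, ANOVA effect and responder cut-off is commonly left to such a plan, and none is shown. Their absence is therefore not the finding. The finding is that sections which are shown state one endpoint and test for power and another for outcome and analysis.

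**A MAS response may be meant.** Section 2.13 says the cited study used MAS, so the rate is plausibly derived from it. That is a fair guess, and the first option under the fix writes it down.

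Three stronger readings are tempting and are not supported:

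- *The trial is underpowered.* The mismatch shows that the power is unknown, not that it is low.
- *The 5% error rate is lost.* Each test keeps its two-sided 0.05. Testing 2 joints × 4 post-baseline visits separately would give a familywise error of 1 − 0.95⁸ = 34% if independent, or about 16% to 30% at common correlations of 0.8 to 0.3. The article plans no such eight tests and no rule that any one of them counts as success.
- *Patients with grade 0 at a measured joint dilute the effect.* Eligibility asks for "symptoms of increased limb muscle tension, with the modified Ashworth Scale (MAS) score grade 1–2" without naming a joint, so such patients could enter. The article gives no share of them, and the argument plays no part here.

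**Conclusion.** The point holds as an inconsistency between stated sections. The 132 per group and 90% power belong to a two-proportion comparison of an undefined effective rate. They do not apply to the only efficacy analysis named. That analysis's power cannot be derived from the document and may be above or below 90%. The reproduction of 132 rests only on the article's own figures. The ranges of 37% to 98%, 46% to 99% and 83% to nearly 100% rest on assumed effect sizes, correlations and time courses, and serve only to show that the two rates do not fix the answer. What is shown is a defect of alignment, cheap to repair; neither a loss of power nor an inflated error rate has been demonstrated.

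**What to change.** Amend the plan before unblinding so that endpoint, test and power statement agree, in one of two ways.

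**(a) Keep the basis of 2.13.** Define the MAS responder rate as the single primary endpoint: one stated grade reduction, one visit (week 4, for example), and one rule for combining or choosing between the measured elbow and knee. Test it once at two-sided 0.05 with a centre-stratified comparison of proportions, since the abstract says randomisation is stratified by centre. Make the repeated-measures analysis secondary. Check that 45.5% and 65% refer to the definition adopted, and restate the power if they do not. If they do, the pooled formula gives 89.4% at 132 per group, and 88.0% at the 126 left after 20% loss (158 × 0.8 = 126.4).

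**(b) Keep MAS grades as primary.** Name one contrast, and replace the 90% statement with the power of that contrast at the planned size, giving the assumed difference, standard deviation and correlation.

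Cost: an amendment to the text, plus a new power calculation under (b). MAS is already recorded at every visit, so neither route needs new data or more patients. Route (a) loses some information by dichotomising. Route (b) may yield a less favourable power figure.

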### Study design

2.1

This study is a randomized, assessor-blinded, Sham-controlled, and parallel clinical trial. From August 2019 to December 2020, we will recruit 316 outpatients or inpatients suffering from limb spasm after stroke, who will be randomly divided into the treatment group (n = 158) and the control group (n = 158) using the central randomized system of clinical research of Guangdong Provincial Hospital of Chinese Medicine in Guangdong. Participants in the treatment group will receive ESA, TJTX, and YNFJ with fixed drug composition and fixed dose, while participants in the controlled group will receive PT.

During the study, we will the participants not to take other drugs that could affect the treatment of spasticity or other treatment methods that might affect the recovery of spasticity during the baseline, treatment, and follow-up periods. The basic drugs for stroke patients (i.e., antihypertensive drugs, hypoglycemic drugs, lipid-lowering drugs, and anti-platelet aggregation drugs) will be permitted. We will evaluate participants during the baseline period and at the second and fourth weeks after randomization (Fig. 1). This protocol will be reported according to recommendations for intervention trials SPIRIT 2013^[19]^ Statement: Defining Standard Protocol Items for Clinical Trials. The test process is designed according to the STICTA 2010^[20]^ report.

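### The 20% dropout allowance was added to 132 (×1.2) rather than divided out (÷0.8), so 158 per arm leaves about 126 and falls short of both 132 and 90% power

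*Protocol article*

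**What the plan says.** Section 2.13 (Sample size calculation) sizes the trial on a total effective rate on the modified Ashworth scale. It takes 45.5% for physical therapy from a published study and 65% for the combined programme from the investigators' early clinical observation. The method is given as "According to comparison of independent sample rates between 2 groups to calculate sample size", with α = 0.05 and β = 0.1, and the result as "power = 90%, 132 participants in each group will be recruited". The next sentence makes the allowance for losses: "Considering an estimated 20% dropout rate, a total size of 158 cases in each group will be recruited".

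The abstract gives the total of 316, and sections 2.1 (Study design) and 2.8 (Randomization and assignment hiding) carry the numbers forward: 158 per group in 2.1, and 316 patients "randomly assigned to the treatment group and the control group according to the ratio of 1:1" in 2.8. Section 2.13 does not say whether α is one- or two-sided, but section 2.15 (Data analysis contents and methods) does: "We will use bilateral test with a significance level of" 0.05.

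**The concern.** Three figures in one section have to agree: the number needed for analysis (132), the dropout rate (20%) and the number recruited (158). They do not. A 20% dropout rate means that one in five recruited patients is lost, so the recruited number multiplied by 0.8 should return 132. It returns about 126. Twenty per cent of the analysed number was added instead of being allowed for as a share of the recruited number.

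What is at stake is whether the power claim is true under the plan's own assumptions. If dropout is as expected, the trial has fewer patients with outcomes than section 2.13 says it needs, and its power for the sizing comparison is below the stated 90%. Dropout is a live issue here: section 2.7 counts as an exit anyone who cannot complete the 6-month follow-up, and the Discussion describes incentives, travel payments and home visits to secure follow-up.

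**Working it through.** **Inputs**

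- Control rate p1 = 0.455, treatment rate p2 = 0.65, difference 0.195 (section 2.13)
- α = 0.05 and power 90% (section 2.13), two-sided (section 2.15), so z = 1.960 and 1.2816
- Allocation 1:1 (section 2.8)
- Dropout 20%, 158 per group recruited (section 2.13)

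**Step 1: reproduce 132.** With unpooled variance,

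n = (1.960 + 1.2816)² × [p1(1 − p1) + p2(1 − p2)] / (p2 − p1)²

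= 10.507 × (0.2480 + 0.2275) / 0.0380 = 131.4, so 132 per group.

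This matches the plan. With pooled variance under the null hypothesis the result is 134.6, so 135. One-sided α gives 110 (pooled) or 107.1, so 108 (unpooled), and does not reproduce 132. The starting figure is therefore acceptable and rests on a two-sided test.

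**Step 2: reproduce 158.** 132 × 1.2 = 158.4, which rounds to 158.

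**Step 3: the allowance that a 20% dropout rate requires.** 132 / (1 − 0.20) = 165 per group, 330 in total. Check: 165 × 0.8 = 132. The plan is 7 per group and 14 in total below this, and 158 is 4.2% below 165.

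**Step 4: what 158 leaves.** 158 × 0.8 = 126.4, so about 126 per group, 6 (4.5%) fewer than 132.

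**Step 5: the dropout rate that 158 can absorb.** 1 − 132/158 = 16.5%.

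**Step 6: power for 45.5% against 65%, two-sided 0.05**

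| Per group | Unpooled | Pooled | Exact, uncorrected chi-square |
|---|---|---|---|
| 126 | 88.8% | 88.0% | 87.9% |
| 132 | 90.1% | 89.4% | 90.2% |

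At 126 per group, all three methods fall below 90%.

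**The case against.** The strongest reply is that the consequence is slight. By the formula that produced 132, power goes from 90.1% at 132 to 88.8% at 126. The 65% assumed for the treatment arm is itself uncertain, and a shift of one or two points is small beside that. This stands as a comment on size. It does not make 158 the right number for a 20% dropout rate.

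A second reply is that 126 counts completers only. Section 2.15 plans an intention-to-treat analysis with multiple imputation, which keeps all 158. The modified Ashworth scale is also measured at weeks 2 and 4, and section 2.13 does not say at which visit the effective rate is taken, so patients lost after week 4 might still contribute. This softens the claim but does not remove it. Imputation does not restore outcomes that were never observed, the per-protocol set takes the loss directly, and the plan made the allowance precisely because it treats dropouts as lost to the sizing calculation.

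A third point is that section 2.15 names repeated-measures analysis of variance for the efficacy data, so neither 88% nor 90% is the power of that analysis. That is correct. The figures here refer to the comparison of two rates, which is the only basis the plan gives for its power.

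Finally, the dropout limit depends on the formula. With pooled variance, 135 per group are needed, and 158 absorbs only 1 − 135/158 = 14.6%. The unpooled formula and the exact calculation at 132 both support 16%. That is a reason to name the method in the corrected text. That 132 comes from the unpooled formula is not a defect.

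**Conclusion.** The concern holds. The dropout allowance is computed wrongly: 158 per group does not preserve 132 after 20% dropout, and nothing elsewhere in the article corrects it. The recruitment figure is 7 per group below what the stated rate requires. At that rate about 126 per group remain, and power is 87.9% to 88.8% instead of 90%.

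This rests on the plan's own inputs: rates of 45.5% and 65%, a two-sided 0.05 test, equal allocation, and dropout read as the share of recruited patients who provide no outcome for the sizing comparison. The arithmetic error is certain. The power loss is about 1 point by the plan's formula and about 2 points by the pooled or exact calculation. It calls for a correction to the stated figures, not a redesign.

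**What to change.** Keep 316 and replace the dropout sentence in section 2.13 with, for example: *With 158 per arm and 20% dropout, about 126 per arm are evaluable, giving about 88% power for 45.5% against 65% (two-sided α = 0.05, exact power of the chi-square test); 90% power holds up to 16% dropout.* If the sponsor prefers the unpooled formula that gave 132, the power at 126 reads 88.8%, about 89%, and the 16% limit is unchanged. Either way, name the method so that both figures come from the same calculation.

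The cost is one sentence and a stated power about 1 to 2 points lower. No patients are added, and sections 2.1 and 2.8 stay as they are.

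If 90% at 20% dropout is to be kept, the alternative is 165 per group: 14 more patients in total, with the totals in the abstract and in sections 2.1, 2.2 and 2.8, and the centre quotas in the abstract, changed to match.
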